## 4. Methods

### 4.1. Trial Design

This is a randomized, double-blind, placebo-controlled, single-case clinical trial in which each subject can be considered as having its own RCT. Twelve subjects with CHD associated with IGR will be screened. Each N-of-1 trial will consist of 3 cycles, including 6 treatment periods, 2 of which are in one group, including 8 weeks of placebo treatment and 8 weeks of Ginkgo biloba. Each subject took Ginkgo biloba drop pills or Ginkgo biloba drop pills simulant at random. There was no washout period at the beginning of the study and there was a 2-week washout period before each treatment period. The entire experimental observation time window is 58 weeks ± 5 days.  Table 1 shows the study design of the subject's medication process. The protocol conforms to the Standard Protocol Items: CONSORT extension for reporting N-of-1 trials (CENT) 2015 [16]. The CENT 2015 checklist can be found in Additional file 2.

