### 4.11. Adverse Events

*(1) Adverse Events (AE)*. Definition: A patient or clinical trial recipient receives a drug after an adverse medical event but does not necessarily have a causal relationship with the treatment. Thus, an adverse event refers to any unanticipated signs associated with the use of a medical (study) product, including laboratory abnormalities, symptoms, or conditions, whether or not medical (study) products are considered. Thus, an adverse event refers to any unanticipated signs associated with the use of a medical (study) product, including laboratory abnormalities, symptoms, or conditions, whether or not medical (study) products are considered.

*(2) Serious Adverse Events (SAE)*. Definition: Severe adverse events refer to the following adverse events at any dose of the test drug or at any time during the observation period, including hospitalization, extended hospital stay, disability, work ability, life-threats or death, and congenital malformations.

*(3) Judgment of Causal Relationship between Adverse Events and Test Drugs*. Adverse reaction evaluation criteria (including symptoms, signs, and laboratory indicators) are as follows.

(1) The time of adverse reactions coincides with the time of administration.

(2) Adverse reactions are associated with known adverse effects of the drug.

(3) Adverse reactions cannot be explained by other reasons.

(4) The adverse reactions are alleviated or disappeared after stopping the drug.

(5) Adverse reactions are reproduced after administration.

*(4) Judgment Criteria for Adverse Events and Drug Relationships*. (1) It is definitely related to: the reaction appears in a reasonable time sequence according to the medication, and it is consistent with the type of reaction known to the suspected drug. The reaction disappears after the suspected drug is stopped, and the patient's clinical state or other reasons are unlikely to produce the reaction.

(2) It may be related to: the reaction appears in a reasonable time sequence according to the medication, and it is consistent with the type of reaction known to the suspected drug. The reaction can be alleviated after the suspected drug is stopped, but the patient's clinical state or other reasons may also produce the reaction.

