(3) It may be irrelevant: the reaction appears to be inconsistent with the reasonable time sequence after administration and does not meet the type of response known to the suspected drug. The response is not alleviated after the suspected drug is discontinued, and the patient's clinical state or other causes may cause the reaction. The response is reduced after the state is improved or after other reasons are eliminated.

(4) It must be irrelevant: the reaction does not meet the reasonable time sequence after administration and does not meet the type of reaction known to the suspected drug. The clinical state of the patient or other reasons can produce the reaction, and the response is relieved after the disease state is improved or other causes are eliminated.

(5) It cannot be judged that there is no clear relationship between the occurrence of the reaction and the time sequence after administration, and the type of reaction known to the drug is similar, and other drugs used at the same time may cause the same reaction.

It is certain that it may be relevant, may be related, and cannot determine three adverse reactions that can be considered as drugs.

*(5) Observation and Recording of Adverse Events*. Subjects with AE should be followed up until the AE recovers (returns to normal or to baseline), or until the condition is stable, or until there is a reasonable explanation.

For AEs that have not recovered at the end of the observation period or AEs that were known at the last visit during the observation period, the investigator should follow up after the visit to return to the above satisfactory results. The necessary treatment, reports, and records should be given as required. For any exceptions, you must go through the consent of the sponsor's security management contact.

*(6) Records and Reports of Serious Adverse Events*. In case of serious adverse events during the trial, the unit undertaking the clinical trial shall immediately take the necessary measures to protect the safety of the subject and report to the local provincial drug regulatory authority and the State Food and Drug Administration, the sponsor within 24 hours. The clinical trial is responsible for the unit ethics committee and informs the participating units. The sponsor will ensure that the reporting procedures for all legal and regulatory requirements are met.

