The SAE collection time for this study ranged from 30 days after the signed informed consent to the last use of the study drug.

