**Study Period**										

		**Enrolment**	**Allocation**	**Post allocation**						**Close-out**

				**Cycle 1**		**Cycle 2**		**Cycle 3**		

	**Time Point**	**D-7 to D-0**	**0**	**Weeks 1-10**	**Weeks 11-20**	**Weeks 21-30**	**Weeks 31-40**	**Weeks 41-50**	**Weeks 51-58**	**Week 58**

**Enrollment**	**Eligibility** **Screen**	×								
	**Informed consent**	×								
	**Allocation**		×							

**Intervention**	**Intervention Ginkgo biloba drop pills or Ginkgo biloba drop pills simulant**			×	×	×	×	×	×	×

**Assessment**	**Baseline variables**	×								
	**Urine pregnancy test for women of childbearing age**	×								
	**Physical examination**	×								×
	**Blood routine, urine routine, liver function, renal function, vital signs, ECG**	×		×						×
	**Blood glucose, blood lipids, SAQ, the angina symptom score, C-reactive protein**	×		×	×	×	×	×	×	×

*Note*. The trial consisted of three cycles and was divided into six treatment periods. Patients receiving Ginkgo biloba drop pills and placebo treatment were randomized. There are 8 weeks for each treatment period and a 2-week washout period at the end of treatment.

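### As worded, the SAE collection window opens 30 days after consent and closes at last use of study drug, contradicting the SAE definition and reporting duty in the same section

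*Protocol article*

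**What the plan says.** Three statements in section 4.11 of the protocol article bear on when an SAE counts.

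- **Definition, item (2).** An SAE is a qualifying event "at any dose of the test drug or at any time during the observation period".
- **Reporting duty, item (6).** "In case of serious adverse events during the trial, the unit undertaking the clinical trial shall immediately take the necessary measures". Reporting is due within 24 hours, and no start day is given.
- **Collection window, closing sentence of the section.** "The SAE collection time for this study ranged from 30 days after the signed informed consent to the last use of the study drug". No other sentence sets a collection window, and none corrects this one.

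Item (5) extends follow-up beyond the last visit, but only for events already on record ("For AEs that have not recovered at the end of the observation period or AEs that were known at the last visit during the observation").

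The calendar comes from section 4.1 and Table 1. Table 1 puts consent and screening at D-7 to D-0 and allocation at 0. Section 4.1 says "There was no washout period at the beginning of the study and there was a 2-week washout period before each treatment period", and "The entire experimental observation time window is 58 weeks ± 5 days". The note to Table 1 says "There are 8 weeks for each treatment period and a 2-week washout period at the end of treatment". Section 4.8 lists visits at baseline and then at week 8, with none between. Section 4.10 names adverse events and SAEs as safety indicators for statistical analysis.

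**The concern.** The closing sentence attaches the 30 days to consent and nothing to the last dose. SAE windows commonly run the other way, from consent to some interval after the last dose, so the wording looks like a transposition. Taken as an instruction, it excludes the opening weeks of each patient's first exposure to blinded study drug and any new event after drug is stopped.

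An SAE on day 10, for example, meets the definition in item (2) and must be reported under item (6), yet lies outside the collection window. Site staff and data managers cannot follow all three statements.

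What is at stake is the completeness of a named safety indicator. There are 12 patients, so one omitted event could change the safety summary. Sample size, randomisation and the efficacy analysis are not affected.

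**Working it through.** **1. Reproduce the plan's calendar.** Six treatment periods of 8 weeks and five washouts of 2 weeks, with none before period 1:

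6 × 8 + 5 × 2 = 48 + 10 = 58 weeks (406 days), of which 48 weeks (336 days) are on treatment.

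This matches the 58 weeks in section 4.1 and the 48 weeks of dosing in the abstract. A washout after period 6 as well would give 60 weeks, so period 6 ends at week 58.

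**2. When the literal window opens.** Opening day = consent day + 30, with dosing taken to start at day 0. That start is an assumption from the Table 1 layout and the absence of an initial washout; counting from day 1 shifts results by one day.

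| Consent | Opens on study day | Share of first 56-day period missed | Share of 336 treatment days missed |
|---|---|---|---|
| D-7 | -7 + 30 = 23 | 23/56 = 41% | 23/336 = 6.8% |
| D-0 | 0 + 30 = 30 | 30/56 = 54% | 30/336 = 8.9% |

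The days between consent and first dose are missed as well. Over 12 patients, the missed treatment time is 12 × 23 = 276 to 12 × 30 = 360 patient-days out of 12 × 336 = 4,032.

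**3. Which treatment falls in the gap.** Section 4.5 randomises order within each cycle in blocks of 2. If both orders are equally likely, about 6 of the 12 patients are expected to be on Ginkgo in the first period. The first visit after baseline is at day 56, so no scheduled visit falls inside the gap. An early SAE first disclosed at week 8 would predate the window.

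**4. When the literal window closes.** It closes at last use of drug.

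- *Completers:* last use and the end of observation both fall at about week 58. What is excluded is new SAEs with later onset.
- *Early discontinuation:* any observation time left after stopping is excluded. As an illustration, stopping at the end of week 18 would leave up to 58 - 18 = 40 weeks outside.
- *Washouts between periods:* these lie inside the window, because last use has not yet occurred.

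**5. Length of the window under the two readings.**

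- Literal: 406 - 30 = 376 days to 406 - 23 = 383 days.
- From consent to 30 days after last use (an assumed reading that the protocol does not state): 406 + 30 = 436 days to 406 + 7 + 30 = 443 days.
- Difference: 60 days, 30 at each end.

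**6. Set against the rest of section 4.11.**

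| Time of a new SAE | Definition, item (2) | Duty, item (6) | Collection sentence |
|---|---|---|---|
| First dose to day 23–30 | Counts | Report | Outside |
| Day 23–30 to last use | Counts | Report | Inside |
| After early stop, still under observation | Counts | Report | Outside |
| After week 58, completer | Not clearly covered | Not clearly covered | Outside |

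The contradiction lies in the first and third rows. The fourth row is a limit of the window, not a conflict between statements.

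**The case against.** The strongest reply is that this is a slip of wording. Other sentences in sections 4.6 and 4.11 are garbled in ways that suggest translation, and it is unlikely that anyone chose to begin SAE collection a month after consent. The 24-hour duty in item (6) has no start day, and section 4.10 lists SAEs as a safety indicator without one. A site that follows those statements loses no early event. This stands as a limit on the size of the problem: the percentages above describe the sentence as written, not a loss known to occur. It does not remove the contradiction, because the faulty sentence is the only one that sets the window.

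A reader might also draw three stronger conclusions, which the document does not support.

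- **That major adverse cardiac and cerebral vascular events (MACCE) would be under-counted.** MACCE is a separate secondary outcome (sections 4.8 and 4.9), and section 4.8 requires efficacy indicators to be recorded at each visit. Nothing ties it to the SAE window.
- **That nothing at all is collected after the final dose.** Item (5) follows unresolved or known adverse events past the last visit, with records and reports. Only new SAEs are left out.
- **That scheduled follow-up after week 58 is lost.** None is scheduled, and for completers the last treatment period ends there.

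Finally, a window ending 30 days after the last dose is a plausible guess at the intent, but no sentence says so.

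**Conclusion.** The concern holds as an internal contradiction in an operative safety rule. Taken literally, the collection sentence leaves out the first 23 to 30 days of dosing, which is 41% to 54% of the first treatment period and 6.8% to 8.9% of all treatment days. It also leaves out new SAEs after early discontinuation or after the final dose. The early gap, and any observation time after an early stop, conflict with the SAE definition and the reporting duty in the same section.

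The figures assume that dosing starts at day 0 and that consent falls within D-7 to D-0. Actual loss depends on sites following the collection sentence over the other two statements, and the document gives no means of judging how likely that is. The point concerns safety ascertainment only.

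**What to change.** Rewrite the closing sentence of section 4.11 so that it agrees with items (2) and (6). SAE collection should start when informed consent is signed and cover at least the whole 58-week observation period, including time after a patient stops study drug early.

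The sponsor should confirm whether the 30 days was meant to run from the last use of study drug and, if so, state it that way. An additional safety contact is not a necessary part of this correction.

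The cost is one sentence in the protocol, with a check that the case report form and site instructions carry the same window. If collection has already begun, sites should be asked whether any SAE between consent and day 30, or after early discontinuation, was left unrecorded.

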### 4.12. Baseline

The baseline data will include demographic data: age, gender, height, weight, ethnicity, and occupation and general clinical data: history, duration, physical examination, comorbidity and medication, and start of trial date.

### 4.13. Statistical Methods

Statistical analysis software will use SAS statistical analysis software version 9.4.

The results were analyzed at the end of the test. The description of the quantitative indicators will calculate the mean, standard deviation, median, minimum, maximum, and interquartile range. The description of qualitative indicators will calculate the number of cases and percentage of each category. All statistical tests use two-sided tests. When the* P* value is less than or equal to 0.05, the difference is considered statistically significant (except where specifically stated). Descriptive statistics will be performed on the completion of the study. Demographics and baseline characteristics will be compared between groups to analyze the balance between the groups.

The analysis of efficacy indicators will use Revman5.0 software for meta-analysis.

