**Methods/Design:**

This is a randomized, double-blind, placebo-controlled, three-period crossover trial for a single subject. A total of 12 subjects will be recruited in this trial. The trial is divided into three cycles, and one cycle has two treatment periods. Ginkgo biloba pills and placebo will be randomized during the treatment period. The test period will last for 58 weeks and subjects will take 48 weeks. Subjects will be selected by the researcher strictly in accordance with the inclusion and exclusion criteria.

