### 4.5. Randomization

With the help of statisticians at Xiyuan Hospital of China Academy of Chinese Medical Sciences, this test will use block randomization, and with a block size of 2. The sequence of test drugs is applied by the SAS random program to generate a “test drug random coding table.” The test drugs were randomly assigned by the database administrator according to the coding table. The prepared research drugs will be delivered, stored, and distributed in the pharmacy of Xiyuan Hospital Clinical Pharmacology Institute. Patients and investigators were blinded to all randomization and packaging procedures until completion of trial. And each subject was randomly assigned to three matched treatment groups, such as BA-AB-BA or AB-BA-BA, in the order in which they were treated.  Figure 1 shows the flow of participants through the trial.

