### 4.8. Efficacy Index

Subjects need to be at baseline, treatment week 8, week 10, week 18, week 20, week 28, week 30, week 38, week 40, week 48, week 50, and week 58 visits. Each visit requires observation and recording of efficacy indicators.

The main evaluation indicators for this trial are the changes in blood glucose and the Seattle Angina Questionnaire (SAQ). The measurement of blood glucose mainly observed the changes of fasting plasma glucose (FPG) and 2 h postprandial blood glucose (2hPG).

The secondary evaluation criteria will be mainly observing the following changes: the incidence of angina symptom scores, C-reactive protein, glycosylated hemoglobin (HbA1c), fasting insulin, blood lipids, metabolomics analysis, and major adverse cardiac and cerebral vascular events (MACCE).

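### The one named efficacy analysis, a RevMan meta-analysis over 12 single-patient trials, does not hold its 5% level under standard per-patient entry; a patient-level analysis should replace it.

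*Protocol article*

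**What the plan says.** All references are to the protocol article.

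- **Section 4.13, Statistical Methods.** "The analysis of efficacy indicators will use Revman5.0 software for meta-analysis". The same section names SAS 9.4, descriptive statistics and a baseline comparison. It says "All statistical tests use two-sided tests" and counts P≤0.05 as significant. It names no other inferential method for efficacy.
- **Section 4.1, Trial Design.** "each subject can be considered as having its own RCT" and "Each N-of-1 trial will consist of 3 cycles, including 6 treatment periods". Each cycle is a pair of periods, "including 8 weeks of placebo treatment and 8 weeks of Ginkgo biloba".
- **Abstract, Methods/Design.** "A total of 12 subjects will be recruited in this trial".
- **Section 4.5, Randomization.** "this test will use block randomization, and with a block size of 2". Each cycle is therefore a randomised pair within the patient.
- **Section 4.8, Efficacy Index.** The visits begin "Subjects need to be at baseline, treatment week 8, week 10, week 18, week 20, week 28, week 30" and continue to week 58. Weeks 8, 18, 28, 38, 48 and 58 close the six treatment periods. The primary measures are fasting and 2-hour glucose and the Seattle Angina Questionnaire.
- **Section 5, Discussion.** The study is described as exploratory and small.

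**The concern.** Inverse-variance meta-analysis was built for studies large enough that each study's variance can be taken as known. Read with the design, the statement in section 4.13 makes each patient a study. Under standard entry, that patient's weight comes from three values per arm (2 df per arm, 4 in total) or from three paired differences (2 df).

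Three things follow:

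- A patient whose few values happen to lie close together receives a very large weight.
- The pooled standard error ignores the uncertainty in the weights.
- The test uses a normal quantile, as if the variances were exact.

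Entering mean, SD and n by arm also discards the pairing that the block randomisation creates.

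At stake are the P values and confidence intervals for the primary measures, since no other efficacy inference is named. None of this is forced on the trial: the investigators hold every patient's data and already name SAS.

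**Working it through.** **Plan's own figure.** The article gives no power or sample-size calculation. The only figure to check is the two-sided 0.05 level.

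**Inputs from the article.** 12 patients (abstract); 3 cycles of 2 periods (4.1); blocks of 2 (4.5); two-sided 0.05 (4.13).

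**Assumptions, because the article gives no SDs.** One end-of-period value per period, so 3 Ginkgo and 3 placebo values per patient; normal errors with within-patient SD 1; no true mean effect; patient-by-treatment SD τ from 0 to 1.

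**Formulas.** For patient i:

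- Effect: yᵢ = mean(Ginkgo) − mean(placebo).
- Unpaired entry: vᵢ = s²G/3 + s²P/3. Paired entry: vᵢ = s²d/3.
- Fixed effect: wᵢ = 1/vᵢ; pooled effect = Σwᵢyᵢ/Σwᵢ; SE = 1/√Σwᵢ; reject if |pooled/SE| > 1.96.
- Random effects (DerSimonian-Laird): the same, with vᵢ plus the estimated between-patient variance.
- Standardised mean difference: Hedges g with its usual variance.
- Comparator: one-sample t-test on the 12 yᵢ, 11 df.

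**Type I error at nominal 5%, 40,000 null trials per setting**

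| Analysis | τ = 0 | τ = 0.5 | τ = 1 |
|---|---|---|---|
| Mean difference, fixed effect | 28.4% | 35.6% | 48.3% |
| Mean difference, random effects | 10.1% | 9.5% | 8.4% |
| Paired, fixed effect | 54.2% | 59.9% | 69.1% |
| Paired, random effects | 12.4% | 10.8% | 9.2% |
| Standardised, fixed effect | 0.4% | 0.9% | 2.1% |
| Standardised, random effects | 0.4% | 0.9% | 1.8% |
| t-test on 12 patient means | 5.0% | 5.2% | 5.0% |

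Further settings added shared cycle effects, unequal patient SDs and serial correlation. Over all settings the unpaired fixed-effect error ran from 17.3% to 48.3%, the standardised analyses from 0.1% to 2.1%, and the t-test from 4.7% to 5.2%.

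**Why it fails (τ = 0).** The unpaired fixed-effect analysis reports a mean SE of 0.177, while the estimate's actual SD is 0.331 (0.177/0.331 = 0.53). A plain average of the 12 yᵢ has true SE √[(1/3 + 1/3)/12] = √0.0556 = 0.236. Estimated weights therefore make the result both less precise than equal weights and overconfident.

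**Variant that nearly works.** If every patient's SE is taken from the pooled within-patient variance (24 df) and entered by generic inverse variance, random effects gives about 4% at τ = 0, rising to about 7–7.5% at τ = 1. Fixed effect with the same SEs gives about 6%, 11% and 23% at τ = 0, 0.5 and 1.

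**Individual intervals, in SDs of the paired difference.** Own variance, 2 df: 4.30/√3 = 2.48. Pooled variance, 12 × (3 − 1) = 24 df: 2.06/√3 = 1.19.

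**The case against.** **The criticised procedure is partly inferred.** The article does not state the effect measure, fixed or random effects, paired or unpaired entry, or the source of the standard errors. Treating the patient as the study is the natural reading of section 4.1 but is not spelled out, and three values per arm rests on using one value per period. A condensed article may leave such details to a fuller plan. This stands as a limit on the size. It does not remove the point, which concerns the method that is named: choosing among the standard per-patient options would not repair it, since none of those tested gave 5%.

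**A stronger reading is tempting: that any RevMan analysis here must be badly wrong, or that the trial will have a false-positive rate of 28% or more.** The documents do not support either. The large inflation needs fixed effect, which is not specified. Random effects on mean or paired differences is about twice nominal, a moderate error. Random effects with externally pooled SEs is compatible with the text and close to nominal.

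**Pooling N-of-1 trials is accepted practice.** Agreed. The objection is only to two-stage pooling with a separate variance from a few values per patient.

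**The study is exploratory.** This lowers the consequence and the rating. It does not repair the intervals, and section 4.13 keeps a significance rule.

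**Conclusion.** The point holds in a conditional form. The one efficacy analysis that the article names is unsuited to 12 single-patient trials of three pairs if patients are entered in the standard way. The error then runs from moderate (about 8–12%, random effects) to severe (28–48% unpaired and 54–69% paired, fixed effect), and goes the other way on the standardised scale (about 2% or less).

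These sizes rest on normal errors, complete data, one value per period and the assumed range of τ. Which of them would apply cannot be read from the article. The patient-level t-test kept its level in every setting tried.

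Rating: should be fixed, in view of the exploratory status in section 5.

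**What to change.** Replace the RevMan sentence in section 4.13 with a patient-level primary analysis in SAS 9.4, using one of these:

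1. **A t-test and 95% interval on the 12 within-patient mean paired differences (11 df).** This is the simplest choice and the one checked by simulation.
2. **A mixed model on the period-level data**, with treatment as a fixed effect, random patient, cycle within patient and patient-by-treatment effects, and Kenward-Roger degrees of freedom. It matches the 11-df t-test only with complete data, no period term and variance components allowed to go negative (NOBOUND). With components bounded at zero, the patient-by-treatment component was estimated as zero in about 53% of null trials and type I error was about 3.4%. The text should say which behaviour is wanted.

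Report individual effects as each patient's mean paired difference, because predictions from the random patient-by-treatment term are shrunken. If intervals use the pooled within-patient variance, say that this assumes equal patient variances, and show own-variance intervals beside them. With unequal SDs (log-SD 0.4), pooled intervals covered only about 84% for the most variable quarter of patients, against 95% with own variances.

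Keep the forest plot as a display only.

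**Cost.** A wording change and a short program, with no new data. Intervals will be wider than RevMan's fixed-effect intervals, which is the price of correct coverage.
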